### 8.3.1.3 Unsolicited adverse events

Severity of unsolicited AEs including immediate AEs (anaphylaxis related) observed within 30 minutes after IP dosing will be classified as follows based on the assessment of severity of local and systemic AEs in healthy adults and adolescents in 「MFDS, Guidelines for the assessment of severity of adverse events in vaccine trials」.

| Grade
Item | Mild
(GRADE 1)                                                                                                                                                            | Moderate
(GRADE 2)                                                                                                                                                                                                                              | Severe
(GRADE 3)                                                                                                                                                                                                                        | Potentially life-
threatening
(GRADE 4)                                                                                                                                                                                                                         |
|-----------------------|--------------------------------------------------------------------------------------------------------------------------------------------------------------------------------------|------------------------------------------------------------------------------------------------------------------------------------------------------------------------------------------------------------------------------------------------------------|----------------------------------------------------------------------------------------------------------------------------------------------------------------------------------------------------------------------------------------------------|--------------------------------------------------------------------------------------------------------------------------------------------------------------------------------------------------------------------------------------------------------------------------------|
| AE term        | 
 
- Temporary or mild discomfort (<48 hours); no medical intervention/treatment required
 
- No impact on daily activities
 
 | 
 
- Mild to moderate restriction on daily activities (able to perform <math>\geq 50\%</math> of usual activities)
 
- May require some help (no or minimal medical intervention/treatment required)
 
 | 
 
- Marked restriction on daily activities (able to perform <50% of usual activities)
 
- Usually requires some help (medical intervention/treatment required, hospitalization possible)
 
 | 
 
- Life-threatening or serious restriction on activities
 
- Requires considerable help (medical intervention/treatment required, hospitalization highly likely)
 
- Serious or life-threatening AE‡
 
 |

‡ A clinical AE considered by the investigator to be serious or life-threatening must be regarded as a grade 4 AE.

Serious or life-threatening AEs include, but are not limited to the followings: convulsion, coma, tetany (symptoms of hypocalcemia such as spasticity or contraction), diabetic ketoacidosis, disseminated intravascular coagulation, petechiae, paralysis, acute psychosis, severe depression.

It should not be confused that AEs or SAEs can both be assessed as severe based on the above definition whereas severe AEs are not necessarily also serious.

\* Enhanced disease refers to a phenomenon that those vaccinated have more serious AEs of viral infection than those unvaccinated. This was identified in the course of development of vaccines such as inactivated respiratory syncytial virus vaccine and dengue vaccine. Enhanced disease is thought to be associated with humoral immune response (antibody-dependent enhancement [ADE]) and cellular immune response (enhanced respiratory disease [ERD]). ADE refers to a phenomenon that non-neutralizing antibodies generated by the vaccine antigens facilitate viral infection via Fcγ receptors (FcγRs) on the cells. ERD refers to excessive invasion of immune cells (e.g., eosinophil) into the lungs of vaccinated individuals due to excessive cellular responses by Th2 (Type 2 Help T).

In the event of AESIs in subjects treated with the IP, additional tests may be conducted as necessary for assessment at the discretion of the investigator, and if necessary, the DSMB may be asked to additionally review the case for status of ADR and enhanced disease.

### 8.3.2 Assessment of causal relationship

In the event of an AE, association with the IP will be assessed by the investigator according to 2-

level criteria: 'related' or 'not-related'.

**(1) Not-related**

An AE that has a temporal relationship to IP dosing which makes a causal relationship improbable, or that can be reasonably explained by other factors rather than IP dosing.

**(2) Related**

All AEs that are not applicable to not-related.

For 'related' AEs, a sub-level of causal relationship can additionally be assessed as necessary.

**① Definitely related**

- Evidence of IP dosing and an AE occurring in reasonable time sequence to IP dosing.
- The event can be most reasonably explained by IP dosing above all possible causes.
- Disappearance of the event upon IP withdrawal and reappearance of the event upon rechallenge.
- The profile of the event is consistent with known information on the IP or drugs of the same class.

**② Probably related**

- Evidence of IP dosing and an AE occurring in reasonable time sequence to IP dosing.
- The event can be more reasonably explained by IP dosing than any other causes.
- Disappearance of the event upon IP withdrawal.

**③ Possibly related**

- Evidence of IP dosing and an AE occurring in reasonable time sequence to IP dosing.
- The event is attributable to IP dosing as much as to other possible causes.
- Disappearance of the event upon IP withdrawal.

**④ Probably not related**

- Evidence of IP dosing.
- There are other more plausible causes of the AE.
- Disappearance of the event or an ambiguous outcome upon IP withdrawal.
- No reappearance of the event or an ambiguous outcome upon rechallenge.

**⑤ Unassessable/unclassifiable**

- The event cannot be judged because information is insufficient or contradictory and cannot be supplemented or verified.

#### **8.4 Reporting serious adverse events**

All SAEs occurring from after the 1st dose of the IP (Visit 2) to the end of study (Visit 11) should be reported, regardless of relationship to the IP, to the sponsor via telephone/fax/email within 24 days from when the event is known to the investigator and to the IRB at the institution within the period defined by the IRB.

AEs occurring after the end of study (Visit 11) will spontaneously be reported by subjects; the investigator will report to the sponsor only serious events that are related to the IP.

To protect subject privacy, the investigator should report SAEs to the sponsor using subject identification codes instead of personal information such as the subject's name, resident registration number, and address. If copies of some medical records are required, personal information except for the identification code will be blocked.

If the investigator obtains additional information about the reported SAE, he/she should submit a follow-up report. The investigator should follow up the SAE on a regular basis until the event is resolved or stabilized or the subject is lost to follow-up and should report to the sponsor and the IRB.

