### 3. Overall study design and plans

#### 3.1 Study design

This study consists of two parts: Part A to evaluate the safety and tolerability of EuCorVac-19 in healthy adults and Part B to evaluate the safety, tolerability, and immune response of EuCorVac-19 in healthy adults.

Amongst individuals who voluntarily provide written informed consent to participation in this study, those eligible based on the inclusion/exclusion criteria will be randomized to a dose level to receive two doses of the IP with 21 days apart and be assessed for safety, tolerability, and immunogenicity according to the following schedules; the study schedules for both Part A and B are same.

| Visit 1   | Visit 2                              | Visit 3           | Visit 4       | Visit 5                              | Visit 6                                | Visit 7                              | Visit 8                               | Visit 9                               | Visit 10                               | Visit 11                               |
|-----------|--------------------------------------|-------------------|---------------|--------------------------------------|----------------------------------------|--------------------------------------|---------------------------------------|---------------------------------------|----------------------------------------|----------------------------------------|
| Day -7~-1 | Day 0                                | Day 2~5           | Day 7         | Day 21                               | Day 2~5 after the 2 nd dose | Day 7 after the 2 nd dose | Day 21 after the 2 nd dose | Day 28 after the 2 nd dose | Week 26 after the 2 nd dose | Week 52 after the 2 nd dose |
| -         | -                                    | -                 | +3D           | +5D                                  | -                                      | +3D                                  | +5D                                   | +7D                                   | ±2W                                    | ±4W                                    |

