##### 3.1.1 Part A

Part A consists of two dose levels (low dose, high dose) of EuCorVac-19. Each dose group consists of 15 subjects in test group and 10 subjects in placebo group.

The first 5 subjects will be randomized and enrolled to the low dose group (Sentinel group: 3 subjects in Test group, 2 subjects in Placebo group); once the safety of the IP is confirmed in these subjects over 7 days after the 1st dose of the IP, the study will proceed to enroll the rest of 20 subjects to the low dose group. The rest of 20 subjects will be randomized to 12 subjects in Test group and 8 subjects in Placebo group. Also, the first 5 subjects will be randomized and enrolled

to the high dose group (Sentinel group: 3 subjects in Test group, 2 subjects in Placebo group); If no Grade  $\geq 3$  adverse drug reactions (ADRs) are reported within 7 days (Day 0 ~ Day 6) after the 1st dose of the IP, the rest of 20 subjects to the high dose group will be enrolled. The 20 subjects in the high dose group will be randomized to 12 subjects in Test group and 8 subjects in Placebo group.

If Grade  $\geq 3$  ADRs are reported within 7 days after the 1st dose of the IP in any of the first 5 subjects (Sentinel group) in each dose groups, the Data and Safety Monitoring Board (DSMB) will review the safety of the IP and determine whether to continue the study. If applicable, subject enrollment will be stopped and additional dosing in the existing subjects suspended until the decision is made on study continuation.

Once the safety results up to 28 days after the 2nd dose are collected from all subjects in Part A, the DSMB will review the safety data from all subjects enrolled in the high and low dose groups in Part A. The DSMB will assess if the event of ADRs in all subjects meet the criteria for study suspension and figure out the relationship between ADR and IP, based on which proceeding to Part B will be decided.

An interim analysis will be conducted using the immunogenicity data collected up to 21 days after the 2nd dose and the safety data collected up to 28 days after the 2nd dose in all subjects enrolled in Part A. Additional interim analysis will be performed using the safety and immunogenicity data collected up to 26 weeks after the 2nd dose in all subjects enrolled in Part A.

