#### **4.2.5 Visit 5 (2nd dose of the IP, 21 + 5 days after the 1st dose)**

This visit will take place on Day 21 after the 1st dose of the IP. Procedures to be carried out during this visit are as follows.

- Any change from the last visit in prior and concomitant medications will be checked.
- The subject diary will be retrieved for status and details of AEs.
- Vital signs will be measured.
- Physical examination will be conducted.
- Pregnancy test will be performed for women of childbearing potential.

- Prior to dosing, a blood sample will be collected for immunogenicity testing and the time of blood sampling will be recorded.
- Contraindications for the 2nd dose of the IP will be checked. If the subject meet the criteria of contraindications for the 2nd dose of the IP, subjects will be treated in accordance with section 5.4 'Criteria for subject discontinuation and withdrawal' and proceeded with the procedure of Visit 9.
- The IP will be administered and the date and time of administration will be recorded.
- The subject will be monitored for 30 minutes post-dose for immediate AEs (anaphylaxis associated).
- The subject will be given a subject diary and instructions on how to complete the diary.
- The next visit day will be scheduled.

If the following symptoms are observed in a subject planned to have the 2nd dose, dosing can be rescheduled within the visit window.

- $\geq 37.5^{\circ}\text{C}$  fever
- Acute infectious disease requiring delayed IP dosing in the opinion of the investigator

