## 5.5 Criteria for study suspension

During the study period, subjects will be monitored for the following ADRs that serve as criteria for study suspension. In the event of ADRs that are the criteria for study suspension, additional enrollment and treatment will be stopped at this time, and the DSMB will meet to decide study continuation.

- 1) Part A study: Grade  $\geq 3$  ADRs occurring within 7 days after the 1st dose in the first 5 subjects
- 2) Part A and Part B studies:
  - ① Grade  $\geq 3$  ADRs occurring within 3 days (Day 0 ~ Day 2) from the respective dosing day and lasting for  $> 1$  day despite active intervention for resolution in  $\geq 15\%$  of all

subjects planned to be enrolled to each study group (Part A:  $\geq 8/50$  subjects, Part B:  $\geq 35/230$  subjects)

- ② SADRs or Grade  $\geq 4$  ADRs occurring within 28 days after the respective dose of the IP

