### **7.3.8 Data and safety monitoring board**

To review study data, the DSMB will be established by the sponsor. Members of the DSMB should ensure the integrity of the study and should not be affected by any factor except when necessary to maintain the safety of study subjects. Individuals who clearly have the financial or intellectual ownership of the IP or applicable procedures or any related conflicts of interest cannot be the members of the DSMB. The DSMB consists of a total of 4 individuals: 3 DSMB members including a chair and 1 administrative secretary. Of those, the 3 DSMB members will have the right to vote: 2 infectiology specialists and 1 statistician. The DSMB administrative secretary will perform administrative tasks for the operation of the DSMB and will not have the voting right. For detailed procedures and information, see 'The Charter of Data and Safety Monitoring Board'.

To determine dose escalation and enrollment status of remaining subjects in each low and high dose group in Part A, 'solicited/unsolicited AEs collected for 7 days after the IP' in the first 5 subjects in the low dose group will be assessed after the end of their Day 7 Visit following the 1st dose of the IP, based on which enrollment of the rest of subjects to the low dose group as well as enrollment to the high dose group will be determined.

In addition, upon the end of Day 28 Visit after the 2nd dose of the IP in the last subject in Part A, 'solicited/unsolicited AEs collected for 28 days after the 2nd dose of the IP' and other safety data obtained from all subjects in Part A will be assessed, verified, and analyzed by the DSMB. The DSMB members will review the adverse events of Part A subjects and assess where those AEs are considered as the criteria for discontinuation of the study. The relation between AE and IP will

also be analyzed and whether to proceed to Part B will be determined.

If DSMB meeting is necessary for review of ADR and confirmation of Enhanced disease in the event of Adverse Event of Special Interest (AESI), DSMB members may analyze the relationship between occurred AESI and IP and confirm whether AESI is Enhanced disease or not.

In the event of AEs that meet the 'criteria for study suspension' during the course of Part A and Part B, the DSMB will meet to assess the safety data and decide on study continuation. However, the placebo group is not subject to review by the DSMB.

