## **8.6 Pregnancy**

Pregnancy in a female subject during the study period is not considered an AE, and hospitalization for elective abortion without complications (therapeutic abortion is not applicable) or for normal delivery of a healthy infant is also not considered an AE.

However, if a female subject becomes pregnant during the study period (Visit 1 to Visit 11), the subject should be withdrawn from the study, and the investigator should complete a pregnancy report and submit it to the sponsor within 24 hours from when the pregnancy is known. Even if the subject stops participating in the study or withdraws from the study, the investigator should follow up and report the course of the pregnant woman and the fetus until childbirth.

Serious complications to the mother, spontaneous abortion, ectopic pregnancy, stillbirth, and death or congenital malformation of the infant will be considered SAEs and should be reported by the investigator according to procedures specified in Section 8.4.

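### Section 8.4 gives investigators 24 days to report any SAE to the sponsor, out of line with Sections 5.5, 7.3.7 and 8.6, so timely study-wide suspension is not guaranteed

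*Protocol*

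**What the plan says.** Section 8.4 covers every SAE from the first dose to Visit 11, whether or not it is related to the product. Each is to be reported "to the sponsor via telephone/fax/email within 24 days from when the event is known to the investigator". Notice to the IRB follows the IRB's own timeline. No shorter limit is given for deaths or life-threatening events.

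Four other sections bear on this clock:

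- **Section 5.5.** One suspension criterion, for both parts, is a serious ADR or an ADR of Grade 4 or higher within 28 days of a dose. When a criterion is met, "additional enrollment and treatment will be stopped at this time, and the DSMB will meet to decide study continuation".
- **Section 7.3.7.** The principal investigator is to tell the sponsor promptly of information that could significantly affect continuation of the study. No number of days is given.
- **Section 8.5.** The sponsor has 7 days for fatal or life-threatening unexpected reactions and 15 days for other SUSARs, both counted from when the event was reported or known to the sponsor. In a multi-site study the sponsor then notifies the other institutions.
- **Section 8.6.** For a pregnancy, which is not itself an adverse event, the investigator must complete a report and "submit it to the sponsor within 24 hours from when the pregnancy is known". Serious pregnancy outcomes are sent back to the Section 8.4 procedure.

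**The concern.** Section 5.5 describes an immediate, study-wide stop. A stop at every site needs someone with study-wide reach to know of the event, and in this protocol that is the sponsor, which sets up the DSMB and notifies the institutions. A serious ADR is an SAE, so the only stated limit on when the sponsor must hear of it is the 24 days in Section 8.4. A site can meet that limit exactly and still leave the sponsor unaware for more than three weeks in what Section 1.2.3 calls a first-in-human trial.

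The ordering is also odd. An uncomplicated pregnancy must reach the sponsor within 24 hours, while a stillbirth or a serious maternal complication, routed through Section 8.4, may take 24 days. At stake are the timing of a suspension and of expedited safety reports. No sample size, power or analysis figure is affected.

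**Working it through.** The 24 days is a stated limit, not a calculated figure, so the check is calendar arithmetic.

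**Inputs**

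- Site-to-sponsor SAE limit: L = 24 days from investigator awareness (Section 8.4).
- Sponsor's limits: 7 and 15 days from sponsor awareness (Section 8.5).
- Event window of the serious-ADR criterion: 28 days after each dose (Section 5.5).
- Second dose: nominally Day 21, as subjects receive "two doses of the IP with 21 days apart" (Section 3.1); window to Day 26 (Section 4.2.5).
- Comparison limit: 24 hours = 1 day (Section 8.6, pregnancy only).

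**Step 1. Investigator awareness to expedited report.** The clocks run one after the other, so the longest compliant time is L + sponsor's limit.

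- Fatal or life-threatening: 24 + 7 = 31 days.
- Other SUSARs: 24 + 15 = 39 days.

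**Step 2. Latest day the sponsor may learn of an event.** This is the day the investigator knows + L, both counted from the relevant dose.

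- Known on Day 0 to Day 6: Day 24 to Day 30.
- Known on Day 28, the last day of the Section 5.5 window: 28 + 24 = Day 52.

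**Step 3. Events certain to reach the sponsor before the same subject's second dose.** The latest qualifying awareness day is the dose day − L.

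- Second dose on Day 21: 21 − 24 = Day −3. No event after the first dose is certain to reach the sponsor in time.
- Second dose on Day 26: 26 − 24 = Day 2. Only an event known by Day 2 is.

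**Step 4. The same sums with L = 1 day, for illustration only.**

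| Quantity | L = 24 days | L = 1 day |
|---|---|---|
| Fatal or life-threatening SUSAR, from investigator awareness | 31 days | 8 days |
| Other SUSAR, from investigator awareness | 39 days | 16 days |
| Event known on Day 28, latest sponsor awareness | Day 52 | Day 29 |
| Latest awareness day that reaches the sponsor by Day 21 | Day −3 | Day 20 |

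**Step 5. Does another section set a shorter limit?** None gives a number for SAEs. The prompt reporting in Section 7.3.7 is unquantified, and that section otherwise refers AE reporting to the protocol, the IRB's rules, GCP and other regulations. The telephone call in Section 8.2 for events of Grade 3 or higher goes from the subject to the site. The bar on a second dose after a related SAE in Section 5.3 protects that subject only. The 24 hours in Section 8.6 is the only other numeric site-to-sponsor limit, and it is for pregnancy.

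**The case against.** A reader might infer that the suspension criteria cannot work, or that a sentinel decision could be taken in ignorance of a serious reaction. The protocol supports neither.

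- **The 24 days is a maximum.** Section 5.5 ties the stop to the event itself, not to receipt of a Section 8.4 report, and sites may report sooner. Sections 5.3, 7.3.7 and 8.2 and the separate IRB notice give further protection. This defeats any claim that suspension must come too late. It does not supply the missing guarantee.
- **The low-dose sentinel gate does not run through Section 8.4.** Under Section 7.3.8, seven days of solicited and unsolicited adverse events "in the first 5 subjects in the low dose group will be assessed after the end of their Day 7 Visit". For the high-dose sentinels, Section 3.1.1 asks whether Grade 3 or higher reactions "are reported within 7 days (Day 0 ~ Day 6) after the 1st dose of the IP", without saying to whom, and Section 3.3.1 holds the other 20 subjects until safety is confirmed. Dependence of that gate on Section 8.4 is not shown.
- **Part A is single-center.** The site that learns of the event is the one enrolling and dosing, so a delay to the sponsor matters least there.
- **Direct comparison of 24 with 7 or 21 mixes clocks.** The 24 days runs from investigator awareness and the other two from the first dose. The differences, 17 and 3 days, are not delays past a gate, and 24 days is shorter than the 26-day outer limit for the second dose.
- **Section 8.6 concerns a different event type.** Its 24 hours makes a slip of unit likely but does not prove one.

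All five points stand, and they limit the finding. None explains why SAEs should have 24 days.

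**Conclusion.** The point holds as an internal inconsistency in an operative safety rule. Section 8.4 lets a compliant site leave the sponsor unaware of any SAE, including a fatal one, for up to 24 days. This conflicts with the stop in Section 5.5, does not fit Section 7.3.7, and is 24 times the limit in Section 8.6. Expedited reports could follow as late as 31 or 39 days after the investigator knew.

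Timely study-wide suspension is therefore not guaranteed. The exposure is mainly in Part B, with 230 subjects at several sites that depend on the sponsor's notice.

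The figures are worst cases: each party uses its full allowance, and in the day counts from dosing the investigator knows of the event on the day named. The clock bears on the Section 5.5 criterion through serious ADRs; a Grade 4 ADR that is not serious falls outside Section 8.4. How fast sites report in practice, and what their SAE instructions say, cannot be seen here.

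**What to change.** The sponsor should confirm the intended unit, correct the 24-day limit in Section 8.4, and check that the corrected limit fits the stop in Section 5.5, the prompt reporting in Section 7.3.7, the sponsor clocks in Section 8.5, and the routing of serious pregnancy outcomes in Section 8.6. If a slip is confirmed, 24 hours is the figure the protocol already uses for a site-to-sponsor report. Any site SAE instructions should be checked for the same wording.

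The cost is small: probably one word in Section 8.4, the usual amendment approval, and a notice to sites. Design, sample size and analysis are unchanged.
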